## Abstract

**Background:**

The advancement of generative artificial intelligence (AI) has shown great potential to enhance productivity in many cognitive tasks. However, concerns are raised that the use of generative AI may erode human cognition due to over-reliance. Conversely, others argue that generative AI holds the promise to augment human cognition by automating menial tasks and offering insights that extend one’s cognitive abilities. To better understand the role of generative AI in human cognition, we study how college students use a generative AI tool to support their analytical writing in an educational context. We will examine the effect of using generative AI on cognitive effort, a major aspect of human cognition that reflects the extent of mental resources an individual allocates during the cognitive process. We will also examine the effect on writing performance achieved through the human-generative AI collaboration.

**Methods:**

This study is a randomized controlled lab experiment that compares the effects of using generative AI (intervention group) versus not using it (control group) on cognitive effort and writing performance in an analytical writing task designed as a hypothetical writing class assignment for college students. During the experiment, eye-tracking technology will monitor eye movements and pupil dilation. Functional near-infrared spectroscopy (fNIRS) will collect brain hemodynamic responses. A survey will measure individuals’ perceptions of the writing task and their attitudes on generative AI. We will recruit 160 participants (aged 18–35 years) from a German university where the research will be conducted.

**Discussion:**

This trial aims to establish the causal effects of generative AI on cognitive effort and task performance through a randomized controlled experiment. The findings aim to offer insights for policymakers in regulating generative AI and inform the responsible design and use of generative AI tools.

Trial registration.

ClinicalTrials.gov NCT06511102. Registered on July 15, 2024. https://clinicaltrials.gov/study/NCT06511102

## Administrative information

Note: the numbers in curly brackets in this protocol refer to SPIRIT checklist item numbers. The order of the items has been modified to group similar items (see http://www.equator-network.org/reporting-guidelines/spirit-2013-statement-defining-standard-protocol-items-for-clinical-trials/).

Role of sponsor {5c}	The funders will have no role in the study design; collection, management, analysis, and interpretation of data; writing of the report; or submission decisions.

## Introduction

### Background and rationale {6a}

Recent advances in generative artificial intelligence (AI) have raised heated debates regarding its use in performing cognitive tasks. Human collaboration with generative AI tools, such as OpenAI’s ChatGPT, has been shown to enhance productivity across a wide range of cognitive tasks, including professional writing tasks among white-collar workers [1], customer support services [2], knowledge-intensive consulting [3], creative story-writing [4], and creative ideation [5]. However, concerns have been raised that heavy use of these tools may lead to the erosion of human cognition [6, 7], which has important implications for human cognitive health [8].

Many prior technological innovations have raised similar concerns about potentially causing a deleterious effect on human cognition and cognitive health. For example, the use of calculators may hinder arithmetic literacy, the use of search engines may reduce aspects of memory skills [9], and the use of social media may contribute to everyday cognitive lapses [10]. According to these concerns, access to these tools may allow individuals to bypass effortful tasks and thus reduce opportunities to engage in the mental practice required for cognitive abilities to fully develop in the human brain [11, 12]. However, technologies could also be seen as an extension of human cognition, or the so-called "extended mind" [13]. With appropriate cognitive offloading, technologies can extend the limits of human cognition and become an active component of human brain mechanisms [14, 15]. For example, the use of calculators can help individuals circumvent tedious arithmetic calculations and focus on complex mathematical problems. The use of search engines can stimulate learning by broadening individuals’ knowledge space and providing tools for self-regulated learning [16]. In the end, the effect of technology tools on human cognition is a nuanced problem that depends on the cognitive task, the tool itself, and how it is used.

The emergence of generative AI tools has again raised heated debates about the effects of the new technology on human cognition due to its significant advancements over its antecedents [17]. These advancements include the following: First, unlike traditional tools that assist with basic skills, such as calculators, generative AI exhibits a higher level of intelligence to create ideas and construct arguments. Second, generative AI encompasses a broad range of cognitive skills rather than a well-defined single one. Consequently, it is difficult to pinpoint which cognitive skills generative AI may affect. Third, generative AI is continuously developing at an ever-increasing speed, which complicates our ability to predict the kinds of cognitive skills it may affect in the future. In consideration of all these advancements and their implications, it is important to evaluate the effects of generative AI tool use on human cognition.

Recent studies have begun to shed light on how generative AI may affect human cognition, mainly through its effects on learning performance outcomes [18]. Randomized controlled trials have found that students performed better when using general-purpose generative AI tools but performed worse when these tools were taken away [19, 20]. This suggests that students may have relied on the tool to bypass cognitive processes essential for developing cognitive skills, which ultimately compromised their performance. A subsequent study has found that generative AI boosted learning for those who use it to engage in deep conversations and explanations but hampered learning for those who sought direct answers [21]. This finding further highlights the difference between using generative AI as an active extension of human cognition and using it merely for passive cognitive offloading.

Studies so far have gained preliminary insights into generative AI’s effects on human cognition and performance through a standard assessment paradigm (SAP) [22]. In their experiments, participants were randomly assigned to either have or not have access to generative AI, and their skills were then tested through task performance in isolation from AI support [19–21]. However, this approach only captures a static snapshot of the *learning product* but is insufficient to understand the ongoing developmental *learning process* during human-generative AI interaction [23]. To gain a deeper understanding of generative AI’s effects on human cognition, it is important to develop measures during the human-generative AI interaction process. In contrast to learning products, the learning process can reveal authentic learning progress over time [24]. Additionally, the SAP tends to focus on performance outcomes but may overlook activities for long-term cognitive development that can be better evaluated through process-based behavioral measures [25, 26].

In light of this background, our study will evaluate the effects of generative AI on task performance and cognitive effort during the human-generative AI interaction process. The task performance will reflect the overall achievement of an individual executing a specified cognitive task in collaboration with generative AI. Cognitive effort will reflect the extent to which the individual actively utilizes their mental resources while performing the task. Exerting cognitive effort is fundamental to training one’s cognitive abilities and maintaining the fitness of the human brain [11]. Measuring cognitive effort during generative AI use allows us to assess whether the technology primarily reduces individuals’ mental exertion or facilitates individuals to invest more effort. We will use state-of-the-art technology to evaluate psychophysiological proxies of cognitive effort throughout the task process in a lab-based randomized controlled trial (RCT). Specifically, we will use an eye tracker to measure pupil dilation changes and a functional near-infrared spectroscopy (fNIRS) to measure cortical hemodynamic activity. Our study context will focus on analytical writing among college students. We choose analytical writing because this task requires high cognitive effort to develop critical thinking [27, 28], a fundamental higher-order thinking skill crucial for problem-solving and decision-making [29, 30]. As important as critical thinking skill is, it remains empirically unclear whether the use of generative AI has implications for the development of this skill.

### Objectives {7}

Our study aims to achieve the following objectives:To establish the effects of generative AI on human cognition and task performance, measured by cognitive effort during the writing process and analytical writing performance (primary objective).To explore the effects of generative AI on subjective perceptions of health and learning-related outcomes.To investigate heterogeneous treatment effects across individuals with different characteristics, such as their motivation to perform well in the writing task, English language ability, writing ability, and critical thinking ability.

### Trial design {8}

Our study is a parallel RCT that compares the effects of using ChatGPT (intervention group) versus not using ChatGPT (control group) in an analytical writing task (Fig. 1). Participants will be randomized in a 1:1 ratio. The study follows an exploratory framework.

**Fig. 1 Fig1:**
[figure not shown]
The trial design with participants randomized into the intervention group and the control group in a 1:1 ratio

The experiment will be conducted on one participant at a time. For each participant, the study consists of three stages. In the first stage, the experimenter will onboard the participant and ask the participant to sign a consent form. In the second stage, the participant will be invited into an experiment room to sit in front of a computer with eye-tracking functionality that collects data on eye movements and pupil size. An experimenter will assist the participant in wearing an fNIRS device that collects data on brain hemodynamic responses. In the third stage, the actual experiment will begin. The participant will independently follow the instructions displayed on the computer screen. The instructions will frame the entire experiment as a writing class that the participant has taken, together with all other participants in the study. To mimic the context in a typical educational setting, the instruction will explain that the participant’s writing score will be graded and ranked among others in the class. The participant will receive their writing score and the class average after the study is completed among all participants.

Within the third stage, the participant will first complete a pre-survey. They will then be instructed to read some materials to learn about analytical writing, and then practice what they have learned by writing an analytical essay as their homework assignment. During practice, the instructions will outline the writing prompt, writing requirement, time requirement, grading feedback, and grading rubric. Specifically, the participant will be asked to write a 350–600-word essay stating whether they agree or disagree with the writing prompt. The time requirement will explain that there is no time limit, but participants are recommended to spend 30 min on the task. We intentionally designed the writing task without a time limit to better reflect a typical homework setting, in contrast to an exam setting where time is constrained. This distinction may elicit different writing behaviors and patterns of using AI tools. For grading feedback, the instructions will explain that the participant will receive their writing score, the class average, and writing feedback from expert instructors once the entire experiment ends. Participants in the intervention group can use ChatGPT to support their writing. Specifically, we choose GPT-4 because it has been independently benchmarked for its standalone performance on analytical writing in the Graduate Record Examinations (GRE), as documented in OpenAI’s technical report [31]. This provides a reference point for us to evaluate the analytical writing capabilities during human-generative AI collaboration. Participants in the control group will complete the writing task without AI assistance. After the writing task, the participant will complete a post-survey. The entire study will last for approximately 1.5 h for each participant.

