### Outcomes {12}

The study has two primary outcomes. First, we will measure participants’ writing performance scores on the analytical writing task. The task is adapted from the Analytical Writing section in the GRE, a worldwide standardized computer-based exam developed by the Educational Testing Service (ETS) [27]. Participants’ writing performance will be scored using the GRE 0–6 rubric and by an automatic essay-scoring platform called *ScoreItNow!*, which is powered by ETS’s e-rater engine [32, 33]. We chose to adapt from the GRE writing materials for two reasons. First, their writing task and grading rubrics were established writing materials designed to measure critical thinking and analytical writing skills and have been used in research as practice materials for writing (e.g. [34]). Second, OpenAI’s technical report shows that ChatGPT (GPT-4) can score 4 out of 6 (~ 54th percentile) on the GRE analytical writing task [31]. This gives us a benchmark for assessing the potential increase in writing performance when individuals collaborate with generative AI.

Second, we will measure participants’ cognitive effort during the writing process. Participants’ cognitive effort will be measured using a psychophysiological proxy—i.e., changes in pupil size [35, 36]. Pupil diameter and gaze data will be collected using the Tobii Pro Fusion eye tracker at a sampling rate of 120 Hz. During the preparation stage of the study, the room light will be adjusted so that the illuminance at the participants’ eyes is at a constant value of 320 LUX. Baseline pupil diameters will be recorded during a resting task in the experiment preparation stage that asks the participant to stare at a cross that will appear for 10 s each on the left, center, and right sections of the computer screen. Pupil diameters and gaze data will be recorded throughout the writing process.

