## Statistical methods

### Statistical methods for primary and secondary outcomes {20a}

Here, the intervention effect on the two primary outcomes will be estimated by an intent-to-treat analysis. Our first primary outcome, writing performance, will be treated as a continuous variable. Our second primary outcome, cognitive effort as measured by mean changes in pupil size, will also be treated as a continuous variable. We will estimate the intervention effect on each outcome separately using ordinary least squares (OLS) regression with heteroskedasticity-robust standard errors. To control for type I error inflation due to multiple testing, we will apply a Bonferroni correction. Accordingly, the adjusted significance threshold is set at *α* = 0.05/2 = 0.025. The outcome of cognitive effort is a psychophysiological measure recorded throughout the entire writing process. Standard pre-processing steps will be taken before the statistical analysis [51, 52], such as correcting for screen angle distortion, removing invalid data that do not reflect the actual pupil size (pupil size below 1.5 mm or over 9 mm [53], often due to blinking), smoothing to remove small oscillatory and noise activity, interpolating blink related invalid data, downsampling, and correcting pupil size changes based on the baseline pupil size that will be collected during a 30-s relaxation task at the beginning of the experiment. Participant-level data will be excluded if the data do not meet basic quality standards, such as having a high proportion of invalid data.

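### Pupil response during the reading stage, taken before the arm-specific screen, would be a cheap precision covariate for the co-primary cognitive-effort outcome, and the plan does not use it

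*Protocol article*

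**What the plan says.** **Order of the session (Trial design {8}).** In the second stage the participant is asked to "sit in front of a computer with eye-tracking functionality that collects data on eye movements and pupil size". The third stage runs from pre-survey to reading to essay: "They will then be instructed to read some materials to learn about analytical writing". The arm difference is introduced at the essay: "Participants in the intervention group can use ChatGPT to support their writing". Intervention description {11a} and Explanation for the choice of comparators {6b} describe it as the right-hand half of the writing screen, which shows ChatGPT in one arm and a basic text editor in the other. No arm-specific version of the reading materials is described.

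**Pupil measurement (Outcomes {12}).** The baseline comes from a resting task in which the participant is to "stare at a cross that will appear for 10 s each on the left, center, and right sections of the computer screen". For the outcome itself, "Pupil diameters and gaze data will be recorded throughout the writing process". The Abstract is broader: "During the experiment, eye-tracking technology will monitor eye movements and pupil dilation".

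**Analysis (Statistical methods {20a}).** Pre-processing includes "correcting pupil size changes based on the baseline pupil size that will be collected during a 30-s relaxation task". The outcome is the mean change in pupil size, analysed by OLS with robust standard errors at a threshold of 0.025. Models are run first without covariates and then with four: self-reported writing, critical-thinking and English ability, and motivation. Improved power is one stated reason for the adjustment. None of the four is a pupil measure.

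**Sizing (Sample size {14}).** The 160 participants are derived from writing performance. The pupil outcome has no calculation of its own; it is argued to be probably adequately powered, partly because it is measured repeatedly.

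**The concern.** Correcting for the resting diameter deals with how large a person's pupil is at rest. It does not deal with how strongly that person's pupil responds to on-screen text and mental work. People may differ in that response whichever arm they are in, and those differences go into the OLS error.

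The repeated-measures argument in Sample size {14} does not remove them. Statistical methods {20a} reduces the pupil series to one mean per participant. Averaging over time shrinks within-person noise, but the test is still a between-person comparison of about 80 against 80.

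The reading stage is an on-screen cognitive task placed before the writing screen, on equipment already set up. A pupil measure from it would be on the outcome's own scale and could be taken before the arms differ. The planned covariates are less well matched to this outcome: all four are self-reports, and Table 2 places the three ability items in the post-survey. At stake is precision on the cognitive-effort question, and so the chance of an uninformative null result.

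**Working it through.** **Inputs from the article.** 160 participants randomized 1:1, so 80 per arm; d = 0.45 with SD standardized to 1 (Sample size {14}, for writing performance); alpha 0.05 in the sizing and 0.025 in the analysis.

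**Assumptions.** Two-sided tests. The article gives no pupil effect size, so d = 0.45 is borrowed from writing performance. It also gives no r, the correlation between reading-stage and writing-stage mean pupil change, so a range is shown.

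**Step 1: the plan's own figure.** By the normal approximation, n per arm = 2(1.960 + 0.842)²/0.45² = 77.5, so 78 (156 in total). The exact noncentral t needs 79 per arm (158 in total) and gives power 0.808 at 80 per arm. The stated 160 for power above 0.8 at alpha 0.05 reproduces.

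**Step 2: the threshold used in the analysis.** At alpha 0.025 and 80 per arm, the noncentrality is 0.45 × √(80/2) = 2.846. Power is 0.720, and the smallest effect detectable with 80% power is 0.491 SD. This is the reference for the next step.

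**Step 3: adding one pre-divergence covariate.** The residual variance becomes 1 − r², so the effective standardized effect is d/√(1 − r²) and the detectable effect is multiplied by √(1 − r²).

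| r | Variance removed (r²) | Noncentrality | Power at d = 0.45 | Detectable d, 80% power |
|---|---|---|---|---|
| 0 | 0% | 2.846 | 0.720 | 0.491 |
| 0.3 | 9% | 2.983 | 0.764 | 0.469 |
| 0.5 | 25% | 3.286 | 0.846 | 0.426 |
| 0.7 | 49% | 3.985 | 0.957 | 0.351 |

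At r = 0.2 power is 0.739. The normal approximation gives 0.727, 0.771, 0.852 and 0.959 for the four rows. A simulation of OLS with HC3 robust standard errors gave 0.83 at r = 0.5 and 0.95 at r = 0.7 with the covariate, against 0.71 to 0.73 without it.

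**Step 4: is the covariate available and clean?** Outcomes {12} names two recording windows, the resting task and the writing process. Reading falls in neither. The broader sentence in the Abstract does not settle the matter. The article also does not say whether the arm-specific pane is hidden while the participant reads. Both conditions therefore have to be secured, not assumed.

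**The case against.** **No error has been shown.** Baseline correction to a resting value is presented as a standard step, an adjusted analysis is prespecified, the trial calls itself exploratory, and further precision covariates may be left to an analysis plan that is not shown. This stands as far as it goes: nothing here is contradictory or biased. But the article itself fixes the baseline, the model and the four covariates, and gives power as a reason for adjusting. A better-matched covariate serves that aim.

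**The data may not exist.** A reader might infer from the seating order and the Abstract that reading-stage pupil data are already being collected and then ignored. The documents do not support this, because the detailed section names only rest and writing.

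**Before divergence is implied, not stated.** Who will be blinded {17a} has the experimenter set the screen format by arm, and Strategies to improve adherence {11c} leaves the participant alone throughout. The pane might therefore be visible during reading. If so, the covariate could be affected by arm, and adjusting for it could introduce bias. Identical materials are likewise only implied. These objections stand, and the fix has to deal with them.

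**The gain is uncertain and measured against a generous reference.** Both change scores would subtract the same 30-second baseline, so error in that baseline alone raises r. Some of the gain could come from adjusting for resting diameter. Reading also differs from composing and typing. What counts is the correlation remaining after the resting diameter and the four planned covariates. This stands and lowers the expected benefit, but does not remove it.

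**The shortfall to 0.72 has another cause.** It comes from sizing at 0.05 and testing at 0.025, which is a separate matter. Accepted: the covariate does not cure that mismatch.

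**Conclusion.** The point holds as a recommendation for a low-cost gain in precision. The randomized comparison is valid without it.

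The size is conditional. At 80 per arm, two-sided alpha 0.025 and an assumed d of 0.45, power moves from 0.72 to 0.76 at r = 0.3, to 0.85 at r = 0.5 and to 0.96 at r = 0.7, with little to gain below 0.3. Neither r nor a pupil effect size is in the article. If r is read as the correlation beyond the resting diameter and the planned covariates, d must be read against the SD that remains after them. The gain would appear in the adjusted analysis only; the unadjusted analysis that precedes it is unchanged.

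It is tempting to say that the trial forgoes the equivalent of 53 participants, since 160/(1 − 0.5²) = 213. That figure rests wholly on r = 0.5, for which the article offers no support, and is only an illustration.

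**What to change.** 1. In Outcomes {12}, state that pupil size is also recorded during the reading stage.
2. In Trial design {8}, confirm that both arms read the same materials, and state that the arm-specific pane appears only after the reading stage ends.
3. In Statistical methods {20a}, add each participant's mean reading-stage pupil change, with the same pre-processing and the same resting baseline, as a prespecified covariate in the adjusted OLS model for the pupil outcome. Keep the existing baseline correction.

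**Cost.** An earlier start of recording on equipment already in place, a check on screen timing, one model degree of freedom, and possibly some missing covariate values where reading-stage data are poor. No extra participants are needed. The recording has to be arranged before sessions are run, because reading-stage data that were not recorded cannot be recovered.
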